## 1. BACKGROUND AND RATIONALE

Premature atherosclerotic cardiovascular disease (CVD) is now a leading cause of morbidity and mortality among persons with HIV-infection. In this population, premature CVD is a consequence of antiretroviral therapy (ART) toxicity, HIV itself, and a higher prevalence of traditional risk factors such as smoking. To date, data are lacking to inform the use of well-tolerated adjunct primary CVD prevention strategies in persons with ART-treated HIV infection.

The positive linear relationship between CVD event risk and low-density lipoprotein cholesterol (LDLc) levels or systolic blood pressure has been well described within general population cohorts, and extends well below the thresholds for lipid or blood pressure (BP) lowering therapy, respectively. Thus, treatment to lower BP and improve lipid profiles among those who would not otherwise receive it could have important health benefits in HIV-infected persons, where CVD risk is higher. In addition, ‘statin’ (HMG-CoA reductase inhibitor) drugs and angiotensin II converting enzyme inhibitors (ACEi) also possess anti-inflammatory and anti-thrombotic properties that may also counter HIV/ART-related mechanisms that promote CVD.

Safe treatments that target traditional CVD risk factors (BP and LDLc) in addition to HIV/ART-related vascular dysfunction, inflammation and thrombogenesis could then be combined to achieve simultaneous reductions in several CVD risk factors. Similar ‘poly-pill’ strategies have been studied in the general population, and would be highly effective at improving medical outcomes for the well over 1 million persons with HIV-infection in the U.S.—50% of whom will be over age 50 by 2015. The focus of this study is to provide pilot data that evaluates the safety and feasibility of a polypill CVD prevention strategy in persons with HIV infection.

### 1.1. Study Goal

Our general goal is to evaluate the feasibility and potential effectiveness of an HIV/CVD polypill in HIV-infected patients with at least moderate CVD risk, by studying candidate drug components (pravastatin and lisinopril) in patients receiving effective treatment with ART that do not require treatment with these medications by current recommendations. In this pilot trial, each participant will be randomized to receive pravastatin 20mg daily versus placebo and lisinopril 10mg daily versus placebo, and followed for 4 months.

### 1.2. Study Hypotheses

- A. Adherence and tolerability to pravastatin (20mg) and lisinopril (10mg), given alone or in combination, will be high in this study population who are, by definition, engaged in care and adherent to their current ART regimens.
- B. Framingham 10 year risk score (FRS) will improve with treatment of either pravastatin or lisinopril due primarily to the effect on blood lipids or BP, respectively.
- C. The potential efficacy of pravastatin (20mg) and lisinopril (10mg), given alone or in combination, will also be assessed via several secondary outcomes: Biomarkers of inflammation, endothelial injury, coagulation, apolipoproteins, lipoprotein particle concentration and large and small artery elasticity (LAE and SAE).

### 1.3. HIV/ART-related CVD Risk

Concurrent with the advent of effective combination ART and a reduction in AIDS events, CVD has become a major cause of morbidity and mortality among HIV-infected patients. Traditional risk factor assessments such as Framingham criteria remain informative for CVD risk among ART-treated HIV-infected patients, but do not incorporate additional risk related to viral replication or ART drug toxicity. Longitudinal cohort data has shown that CVD event risk increases with each additional year of protease inhibitor (PI)-based ART, after adjusting for additional factors including lipids. This pilot study will focus on treated HIV-infected participants with moderate CVD risk, assessed from Framingham risk score cutoffs and incorporating duration of PI exposure.

In the general population, mechanisms that promote atherosclerosis, in part, involve inflammation, thrombogenesis, adverse lipid and metabolic changes, and vascular damage and dysfunction. These same factors are amplified among individuals infected with HIV, whether related to viral replication, ART use, or the increased prevalence of smoking.

HIV infection and ART each have a substantial impact on blood lipids. Among men in the Multicenter AIDS Cohort Study (MACS), HDLc, and LDLc decrease following HIV seroconversion. Triglyceride levels (TG) are elevated with HIV infection, when compared to HIV-negative cohorts. Starting ART is associated with a typical metabolic pattern including hypertriglyceridemia, hypercholesterolemia, lipodystrophy and alterations of glucose metabolism. Specifically, ART initiation among HIV-infected patients in MACS led to increases in total cholesterol (TC) and LDLc above pre-infection levels, while HDLc remained approximately 10mg/dl below pre-infection levels.

Strong evidence linking HIV- and ART-related increases in inflammation and thrombogenesis, and subsequent CVD risk, has come from recent studies of plasma specimens from SMART. Higher baseline levels of IL-6 and D-dimer were strongly associated with an increase mortality risk (IL-6 OR = 8.3, 3.3-20.8; D-dimer OR = 12.4, 4.2-37.0), and associations persisted for both CVD and non-CVD death. A follow-up comparison of baseline biomarker levels in SMART participants with general population cohorts, including the Coronary Artery Risk Development in Young Adults (CARDIA) study and the Multi-Ethnic Study of Atherosclerosis (MESA), and found that hsCRP, IL-6 and D-dimer levels were 50-100% higher in HIV-infected participants both on and off ART ( $p < 0.001$  for all). Thus, pro-inflammatory mechanisms persist in persons with HIV infection even after starting ART.

Endothelial function in persons with HIV infection may be a consequence of inflammation, HIV replication itself, and/or ART drug toxicity. Endothelial cell adhesion molecules are elevated in persons with HIV infection, when compared to HIV negative controls. Brachial artery flow mediated dilation (FMD) was impaired among 75 HIV infected participants when compared to an historic cohort of 223 HIV negative controls, and was associated with a detectable HIV RNA level. We have also demonstrated that LAE and SAE is impaired among persons with untreated HIV infection compared to HIV-negative controls, after adjusting for additional risk factors including Framingham risk score. Treatment with lisinopril and pravastatin in this proposal may counter mechanisms related to inflammation and vascular dysfunction.

### 1.4. Blood Pressure and Lipid Lowering Treatment to Reduce CVD Risk

High BP and cholesterol cause more than half of all CVD globally. Data from over 350,000 men part of the Multiple Risk Factor Intervention Trial (MRFIT) demonstrated a strong continuous CVD risk gradient with SBP and TC levels that extends below diagnostic thresholds for 'hypertension' or 'hypercholesterolemia', and risk across the board is amplified by smoking. Data from large trials have confirmed the benefits of BP and lipid lowering treatment, with ACEi and statin drugs respectively, in moderate to high-risk patients who do not have 'hypertension' or 'hypercholesterolemia'.

Recent findings from the Justification for the Use of Statins in Prevention: an Intervention Trial Evaluating Rosuvastatin (JUPITER) demonstrate that pre-emptive treatment with a 'statin' (HMG-CoA reductase inhibitor) medication reduced CVD events among persons with elevated hsCRP levels. In JUPITER, a 50% reduction in CVD events was reported among 17,802 participants with elevated hsCRP levels ( $\geq 2\text{mg/L}$ ) and LDLc  $< 130\text{mg/dL}$  given a Rosuvastatin medication. Whether a result of the 50% reduction in LDLc or the 37% reduction in hsCRP levels, the clinical benefit of pre-emptive statin treatment in this population with moderate CVD risk has direct implications for prevention strategies among HIV-infected persons. In addition, a recent study of 76 patients with a BP  $< 140/90$  mmHg, treatment with an angiotensin receptor blocker led to a 30% improvement in small artery elasticity, as well as lowering BP. The use of ACEi or statin medications as primary prevention specifically among HIV-infected patients without 'hypertension' or 'hypercholesterolemia' has not been reported.

## 2. METHODOLOGY

### 2.1. Study Design

This proposal will study the tolerability and potential efficacy of pravastatin 20mg once daily and lisinopril 10mg once daily to reduce CVD risk among at least 40 HIV-infected patients receiving effective ART. A double blind, randomized, 2x2 factorial design will be utilized to compare each study with a matched placebo pill. After screening, 3 study visits are planned: baseline, month 1 and month 4.

#### Study Population

##### Inclusion Criteria:

1. HIV-infected participants receiving ART with HIV RNA level  $< 400$  copies/mL, and
2. Framingham 10yr risk score  $\geq 3\%$

##### Exclusion Criteria:

- 1) Known CVD or CVD equivalent (including DM or Framingham 10yr risk score  $> 20\%$ )
- 2) Unable to obtain a pulse waveform measure (e.g. due to atrial fibrillation)
- 3) Currently taking a statin, ACEi or antitensin receptor blocker
- 4) BP  $\geq 140/90\text{mmHg}$  at screening visit (the lowest of 3 values may be used)

[figure not shown]

- 5) LDL cholesterol  $\geq 160$ mg/dL with Framingham 10yr risk score  $< 10\%$
- 6) LDL cholesterol  $\geq 130$ mg/dL with Framingham 10yr risk score 10-20%
- 7) TG  $> 500$ mg/dL (must first treat to  $< 500$ mg/dL)
- 8) History of cirrhosis or current ALT/AST  $\geq 5 \times$  the upper limit of normal
- 9) Chronic kidney disease with a creatinine  $\geq 2.0$  mg/dL
- 10) Contra-indications to any of the study drugs (or an angiotensin receptor blocker)

#### Intervention:

All participants will be randomized to take pravastatin 20mg daily or matched placebo, and lisinopril 10mg daily or a matched placebo, for 4 months. This is summarized in figure above.

## **2.2. Outcomes**

### Primary Outcomes

- a. Medication tolerability
  - i. Study withdrawal due to medication side effect (subjective or lab criteria)
  - ii. Discontinuation of a single study medication due to side effect (subjective or lab criteria)
  - iii. Lab measure with  $> 2$  fold increase (with emphasis on: Creatinine, CK, AST, ALT)
- b. Adherence to study medication
  - i. Self report of misses per week
  - ii. Pill count by study RN – reported as % (pills taken/days enrolled in study)
- c. Changes in Framingham risk score (FRS), including serum cholesterol levels and blood pressure

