## **2.4. Data Collection**

Details of study will be reviewed with all interested participants. If inclusion criteria are likely based on review of clinic records then a screening visit may be scheduled, where labs and BP will be assessed. Informed consent will be obtained at screening visits. Screening blood draw results will be used to verify blood lipid eligibility criteria (LDLc and TG). The lowest BP reading, taken from up to 3 readings during a screening visit, may be used to assess eligibility criteria. Participants will be given an information pamphlet on ways to reduce heart disease risk at enrollment. If exclusion or withdrawal criteria are met due to BP or lipid level thresholds, then a note with these results will be sent to the participants primary care giver with recommendations that they be evaluated for hypertension or dyslipidemia, respectively.

If eligibility criteria are met, participants will be randomized at the baseline visit to occur within 2 months of screening/consent. After enrollment and baseline visit, participants will present month 1 and month 4 for repeat study procedures. The visit schedule is outlined in the table below. Visits will last approximately 60 minutes.

Toxicity labs and a clinical assessment will be scheduled at any point during the 4 months follow-up if new symptoms develop that may be related to study medications. Toxicity labs and adherence will otherwise be assessed along with study procedures at scheduled 1 and 4 month visits.

**TABLE:** Study procedures and visit timeline

| Measure                      | Screening visit            | Baseline visit       | Symptoms? | Month 1 visit | Month 4 visit |
|------------------------------|----------------------------|----------------------|-----------|---------------|---------------|
| Informed consent             | X                          |                      |           |               |               |
| Randomization                |                            | X                    |           |               |               |
| BP                           | X                          | X                    |           | X             | X             |
| Lipids (TC, HDLc, LDLc, TG)  | X                          | X (if not at screen) |           | X             | X             |
| FRS                          | X                          | X                    |           | X             | X             |

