| Med Adherence                |                            |                      | X         | X             | X             |
| Hep B/C serologies           | X                          | X (if not at screen) |           |               |               |
| Toxicity labs (CMP, CBC, CK) | X                          | X (if not at screen) | X         | X             | X             |
| HIV labs (RNA, CD4)          | X (if not $\leq 3$ months) | X (if not at screen) |           | X             | X             |
| Artery Elasticity            |                            | X                    |           | X             | X             |
| Biomarkers                   |                            | X                    |           | X             | X             |
| Stored Specimens             |                            | X                    |           | X             | X             |

Randomization will be predetermined using block-randomization with varied groups of 4 and 8, and blinded to investigators, staff and participants. An un-blinded statistician, one research staff not involved with study visits, and an HCMC pharmacist will have access to the randomization code.

Pravastatin and lisinopril will be purchased through HCMC pharmacy at reduced generic pricing. Active study drugs and placebo pills will be encapsulated (Custom-Rx Compounding Pharmacy in Richfield, MN) and then packaged and labeled with a study identification number. Study medications will be stored and dispensed by study investigators. Investigators will comply with HCMC policies on use of medications for ongoing IRB approved studies.

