## 2.6. Study procedures

At study visits participants will be assessed for study medication tolerability and toxicity, undergo a peripheral blood draw, and BP and artery elasticity measurements. Demographic characteristics, past medical history and additional risk factors will also be ascertained. Framingham 10-year risk score will be calculated using an NHLBI online algorithm (<http://hp2010.nhlbi.nih.net/atpiiii/calculator.asp>), after entering age, gender, smoking status, TC, HDLc, systolic BP and use of a BP lowering medication.

Medication tolerability: At each visit, subjective symptoms will be assessed along with toxicity labs will be assessed at each visit. Clinical assessment and toxicity labs will also be measured outside the context of study visits if participants develop subjective side effects that may be related to study medications.

Toxicity labs include:

- i. Complete blood count (CBC)
- ii. Complete metabolic panel (CMP: including liver function tests)
- iii. Creatine phosphokinase (CK).

Adherence: Adherence will be assessed via participant report and pill count (by study RN) during follow-up visits.

Arterial Elasticity Measurements: Arterial elasticity will be assessed via pulse waveform analysis (model PulseWave CR-2000, Hypertension Diagnostics, Inc., Eagan, MN), which provides the following measurements: large and small artery elasticity index (ml/mmHg; LAE and SAE respectively), systemic vascular resistance ( $\text{dyne} \cdot \text{sec} \cdot \text{cm}^{-5}$ ), total vascular impedance ( $\text{dyne} \cdot \text{sec} \cdot \text{cm}^{-5}$ ), cardiac output (L/min), pulse rate (beats/min), and BP (mmHg). Measures will be assessed in triplicate.

Procedures for obtaining artery waveform measurements are described in the device operator's manual. Participants will be instructed to fast and avoid caffeine, nicotine, anti-histamines and NSAIDS prior to study visits.

Blood pressure: Blood pressure will be assessed during artery elasticity waveform measures, and estimates will also be ascertained in triplicate.

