## 4. ANALYSIS PLAN

The general goal of this pilot study is to gather feasibility and efficacy data, utilizing a 2x2 factorial design (4 cells of  $n=10$ ,  $n=40$  total), to inform planning for a multi-center HIV/CVD polypill trial. We believe treatment with pravastatin (20mg daily) and lisinopril (10mg daily) will be well tolerated and be well adhered to by participants engaged in care and already adherent to ART. We hypothesize that Framingham risk score will improve with either drug intervention. Future sample size estimates will be generated from effect size related to changes in arterial elasticity and biomarkers.

**Primary Analyses:** Mean changes in FRS after 4 months will be studied with pravastatin use (versus placebo) and lisinopril use (versus placebo). The effect of both drugs combined, compared with double-placebo, will also be examined. Adherence and the frequency of intolerability, based on subjective or lab criteria, will also be compared between groups using the definitions listed in ‘outcomes’ (2.2). Elevations in lab values will also be categorized by severity (using established grades 1-4).

**Secondary Analyses:** Mean changes in hsCRP, IL-6, D-dimer, SAE, ApoB, ApoA1, and LDL and HDL particle concentrations will be studied after 4 months of pravastatin and lisinopril, given alone or in combination, using similar methods as above in primary analyses. Tests for correlation between change in these markers and BP, total cholesterol and FRS will also be considered. Regression models may be

considered to adjust for additional clinical characteristics (including, but not limited to traditional CVD risk factors), but power will be quite limited for these analyses.

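### Primary tolerability counts laboratory harm only as a more than two-fold rise, so lisinopril-type effects that do not lead to stopping may be under-counted

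*Combined protocol and SAP*

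**What the plan says.** Section 2.2 lists three components of medication tolerability under the primary outcomes:

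- a.i: "Study withdrawal due to medication side effect (subjective or lab criteria"
- a.ii: "Discontinuation of a single study medication due to side effect (subjective or lab criteria"
- a.iii: a laboratory measure with a more than two-fold rise, worded "fold increase (with emphasis on: Creatinine, CK, AST, ALT"

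BP appears among the primary outcomes only under item c, with the risk score: "Changes in Framingham risk score (FRS), including serum cholesterol levels and blood pressure".

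The toxicity panel in the visit table (section 2.4) is "Toxicity labs (CMP, CBC, CK". Section 2.6 describes one part of it as "Complete metabolic panel (CMP: including liver function tests" and does not list the other analytes. For unscheduled visits, section 2.4 says "Toxicity labs and a clinical assessment will be scheduled at any point during the 4 months follow-up if new symptoms develop". In the table, the 'Symptoms?' column is marked for adherence and toxicity labs and is blank for BP.

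Section 4 compares intolerability between groups using the section 2.2 definitions and adds: "Elevations in lab values will also be categorized by severity (using established grades 1-4". Section 3.2 un-blinds participants and stops active drug when toxicity is suspected clinically or when a listed criterion is met. The listed criteria cover transaminases, CK, creatinine, high BP and a new indication for treatment.

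**The concern.** A doubling is a workable event definition for an enzyme such as CK or a transaminase. It is a poor one for an analyte held in a narrow range, and it cannot register harm that shows as a fall, although a blood count is drawn as a toxicity lab. BP is lowered on purpose in people who enter below 140/90 mmHg, yet no tolerability item uses a low reading.

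The two drugs are therefore not measured evenly. Hypothesis A in section 1.2 predicts high tolerability for each drug, alone or combined, and section 4 says the results will inform a multi-center trial. If milder lisinopril effects are counted less readily than milder pravastatin effects, the comparison of the two tolerability profiles tilts towards lisinopril.

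**Working it through.** **The plan's own figure.** No calculation is given for tolerability. The only design calculation (section 2.5) is 20 per group for a 0.9 SD difference in risk score, with 80% power at two-sided 0.05. It reproduces: n = 2 × (1.96 + 0.84)² / 0.9² = 19.4, rounded up to 20 per group. Power at 20 is 81.2% by the normal approximation and 79.2% by the t-test. Nothing below changes it.

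**What a.iii can register.** I read the fold as relative to baseline, which a.iii does not state. The threshold is then more than 2 × baseline. All baselines are assumptions.

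| Analyte | Assumed baseline | Needed to count |
|---|---|---|
| Potassium, mmol/L | 3.5 / 4.0 / 5.0 | >7.0 / >8.0 / >10.0 |
| Creatinine, mg/dL | 0.8 / 1.0 / 1.2 | >1.6 / >2.0 / >2.4 |
| Any blood count, falling | any | cannot count |
| BP | any | not a laboratory measure |

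Potassium would almost never qualify. Creatinine can.

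**Routes into the primary outcome, side by side.**

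| Event | Without stopping (a.iii) | With stopping (a.i, a.ii) | Section 4 grading |
|---|---|---|---|
| CK, AST or ALT doubling | yes | yes | yes |
| Creatinine doubling | yes | yes | yes |
| Potassium rise | practically no | yes | possibly, if the panel reports it |
| Blood-count fall | no | yes | no |
| Low BP | no | yes, in practice through its symptoms | no |

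For AST and ALT the contrast is softened, because section 3.2 also makes a doubling from baseline a reason to un-blind and stop active drug. For CK the section 3.2 criterion is above 4 times the upper limit of normal, so a smaller CK doubling can count through a.iii alone.

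**Scale.** One participant in a group of 20 is 1/20 = 5 percentage points. If 5%, 10% or 15% of those on lisinopril (assumed) had such an event and none stopped drug, 0.05 × 20 = 1, 0.10 × 20 = 2 or 0.15 × 20 = 3 would be missed. These are ceilings, because those who stop are counted. For comparison, 0 events in 20 leaves a one-sided 95% upper limit of 1 − 0.05^(1/20) = 13.9%. By Fisher's exact test, 3/20 against 0/20 gives p = 0.23, and the smallest split against zero below 0.05 is 5/20 (p = 0.047). Missed events of this number would change the reported proportion rather than the result of a test.

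**The case against.** A reader might infer that potassium, low BP and blood-count events can never count, that the outcome was shaped for statin toxicity, and that lisinopril will look tolerable by construction. The documents do not support any of these.

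- Components a.i and a.ii have no fold threshold, no direction and no analyte list. Section 3.2 stops active drug on clinical suspicion of toxicity alone. Symptomatic low BP attributed to study drug would usually be counted that way.
- Symptoms are assessed at every visit (section 2.6), and lisinopril symptoms that lead to stopping count against it.
- Creatinine heads the emphasis list in a.iii and has its own criterion in section 3.2. The emphasis wording does not confine a.iii to four analytes.
- The section 4 grading sits in the primary analyses and needs no doubling, so a potassium elevation could appear there.
- The blank BP cell does not show that a dizzy participant would have no BP taken. A clinical assessment is required at symptom visits, its content is unspecified, and the table has no row for it at any visit. BP is also measured at months 1 and 4.

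All of this stands, and it limits the point to events that do not lead to stopping. It does not remove the point: the grading omits falls and BP and is not part of the section 2.2 definition, and no tolerability item uses the BP values collected.

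**Conclusion.** The point holds as a low-cost improvement to a primary outcome definition. Under the stated rule, CK, AST and ALT doublings count regardless of stopping. Potassium rises, blood-count falls and low BP enter the primary outcome only through withdrawal or discontinuation, with a possible further trace of potassium in the section 4 grading. Lisinopril intolerability short of stopping may therefore be under-counted relative to pravastatin.

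The size cannot be derived from the documents, which give no event rates and no stopping probabilities. The 1 to 3 of 20 above is an illustration on assumed rates. The conclusion also assumes that the metabolic panel reports potassium and that a potassium rise is a relevant lisinopril effect; the documents state neither. The documents do not tie blood-count falls to lisinopril, so that gap applies to either drug. It would go too far to say that a clean lisinopril result would be an artefact of the measure.

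**What to change.** Amend outcome a in section 2.2 and align section 4 and the visit table with it:

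1. Keep the more than two-fold criterion for CK, AST, ALT and creatinine, and state that the reference is baseline.
2. Add the grade 1 to 4 scale already named in section 4, naming its source. Apply it as worsening from baseline in the harmful direction for the metabolic-panel and blood-count analytes, with potassium named.
3. Mark BP in the 'Symptoms?' column of the visit table as a recorded measurement.
4. Report low BP, and symptoms with a concurrent low BP, descriptively by group as a tolerability item. The study team should write down beforehand what the report will call low.

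The laboratory values and scheduled BP readings are already collected, so the cost is a change of wording plus one cuff reading at unscheduled visits. The sample size is unaffected. The downside is that more minor changes will be reported, and observed tolerability may look slightly less favourable. These are definitions for counting and reporting; no stopping rule or clinical threshold is proposed.

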### 3.2. Participant Safety Monitoring and Withdrawal

Participants will undergo clinical assessment for side effects to study medication at baseline and each follow-up visit (months 1 and 4). Toxicity labs will be assessed per 2.6 above at each study visit, or at any point during the study if symptoms suggestive of drug toxicity/intolerance develop. A clinical pharmacist will participate on protocol team (i.e., [name]) and will review the active clinical medication list upon request for participants prior to enrollment – where potential drug-drug interactions will be identified. Participants taking darunavir (which may increase pravastatin levels to a greater extent than other PIs) will not be excluded from participating from the study, but if a trend is suspected toward more toxicity in these participants then darunavir use may be added to exclusion criteria. Participants may withdraw from the study at any time at their request, as described in the consent.

Participants will be un-blinded to study medication (and will stop any active drug) if toxicity is clinically suspected, or if any of the following criteria are met:

- i. ALT/AST levels double from baseline, increase to  $\geq 10$  x upper limit of normal, or any elevation associated with clinical symptoms.
- ii. CK increase to an absolute level of  $>4$ x upper limit of normal
- iii. Serum creatinine increase  $>0.5$  mg/dL and to an absolute level  $>2.0$  mg/dL; if only one of these criteria are met toxicity labs will be repeated in 2 weeks.
- iv. Blood pressure  $>140/90$ mmHg at baseline and month 1 (lowest value may be used at each visit), when a participant fulfilled the BP thresholds/requirements at screening visit
- v. New clinical indication for ACEi or statin medication that was not present at enrollment

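### The pill-count adherence formula does not say per drug or pooled, and its days-enrolled denominator scores a protocol-directed stop as missed doses in anyone who stays enrolled

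*Combined protocol and SAP*

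**What the plan says.** In the combined protocol and SAP, section 2.2 lists "Adherence to study medication" as primary outcome b. It has two parts: self-reported missed doses, and a nurse pill count "reported as % (pills taken/days enrolled in study", with days enrolled closing the ratio. The numerator is not tied to either drug.

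The regimen has two products. Section 2.1 (Intervention) reads: "All participants will be randomized to take pravastatin 20mg daily or matched placebo, and lisinopril 10mg daily or a matched placebo, for 4 months". Section 2.1 (Study Design) gives the frequency as "pravastatin 20mg once daily and lisinopril 10mg once daily", each compared "with a matched placebo pill". The products are encapsulated (section 2.4), and outcome a.ii counts stopping one of them alone. Two separately removable capsules a day is therefore the natural reading, but no section gives a capsule count.

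On stopping, section 3.2 says that a participant with suspected toxicity, or who meets one of its listed criteria, is un-blinded "and will stop any active drug". Section 2.3 (Study Drug) says the same for toxicity. Section 2.6 adds no rule for calculating adherence. Section 4 compares adherence between groups by referring back to the definitions in section 2.2.

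**The concern.** Two things are left open in a primary outcome formula.

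- **Numerator.** With two products a day, pills over days means one thing if calculated per drug and another if both drugs' pills are added together. At full use the two readings differ two-fold. Only the per-drug reading separates adherence to one drug from adherence to the other, and hypothesis A in section 1.2 concerns each drug, alone and combined.
- **Denominator.** Days enrolled are not the same as days on which the participant was supposed to take the product. After a directed stop with continued enrolment, every remaining day counts as a missed dose.

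The second point matters on either reading. It moves tolerability, which is outcome a, into adherence, which is outcome b. It does so mainly where active drug was assigned, because that is the drug the text orders stopped. The pilot is meant to supply feasibility data for a multi-center trial, and an adherence figure that mixes missed doses with directed stops is hard to use for that purpose.

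**Working it through.** The plan gives no numerical adherence figure to reproduce. Its one power statement (section 2.5: 20 per group, 0.9 SD, 80%) concerns Framingham risk score. It reproduces at 81.2% by the normal approximation and 79.2% by the two-sample t-test, and nothing below affects it.

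**Inputs**
- Formula: pills taken / days enrolled (section 2.2, b.ii).
- Two products, each once daily (section 2.1). One capsule per product per day is an inference.
- Follow-up of 4 months, taken as 120 days (assumption).
- 20 per group for each drug comparison (section 2.5); cells of 10 (section 4).
- Stop at day 30 (assumption), near the month 1 visit, where the first toxicity labs after baseline are scheduled.

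**The formula under each reading (drugs A and B)**

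| Case | Pooled pills / days | Per drug, A and B | Pooled pills / (2 × days) |
|---|---|---|---|
| Full use of both | 240/120 = 200% | 100%, 100% | 240/240 = 100% |
| A fully, B never | 120/120 = 100% | 100%, 0% | 120/240 = 50% |
| Half of each | (60 + 60)/120 = 100% | 50%, 50% | 120/240 = 50% |
| 90% of each | (108 + 108)/120 = 180% | 90%, 90% | 216/240 = 90% |
| A fully, B perfectly to a directed stop at day 30 | (120 + 30)/120 = 125% | 100%, 25% | 150/240 = 62.5% |

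The first four rows do not depend on the choice of 120 days. Rows two and three show that either pooled version gives one score to two different patterns of use. The per-drug ratio separates them and is correct at full use.

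The last row goes wrong in every column. The participant missed no dose that was due. Counted over assigned days, drug B scores 30/30 = 100%.

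**Effect on a group mean, per-drug reading**
- Loss for one participant: 100 − 25 = 75 points.
- Group of 20: 75/20 = 3.75 points per case. Cell of 10: 75/10 = 7.5 points per case.
- Range by stop day, group of 20: day 60 gives 60/120 = 50%, a loss of 50/20 = 2.5 points; day 90 gives 90/120 = 75%, a loss of 25/20 = 1.25 points.
- Range by number of day-30 stops, group of 20: one gives 3.75 points, two give 7.5, three give 11.25.

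If the participant is withdrawn at day 30 and enrolment ends, the stated formula itself gives 30/30 = 100% per drug and there is no loss.

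**The case against.** The strongest reply is that dividing by days makes sense only for one pill a day, so the formula must have been meant per drug. Section 2.3 says the factorial design allows each treatment to be evaluated separately, and outcome a.ii already tracks single drugs. This stands. A reader might infer that the plan will report 200% for a fully adherent participant, but the text does not say that pills are pooled. Even if they were, doubling applies to every group, so by itself it would not bias a comparison, and a value near 200% would be noticed. Pooling would still hide which drug was missed.

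On the denominator, a reader might infer that enrolment days always run on after a stop. The documents do not say so. The stopping rules sit in a section that also covers withdrawal, and section 2.4 speaks of withdrawal criteria for blood pressure and lipid thresholds. For a participant who is withdrawn, the problem may vanish. It remains for those who stop one drug and stay in the study. Section 2.2 foresees that case by listing single-drug discontinuation (a.ii) apart from study withdrawal (a.i).

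A reader might also infer that only active arms can be penalised. Section 3.2 directs the stopping of active drug but is silent on whether an un-blinded participant continues placebo, so the direction is a tendency and not a certainty.

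Finally, stops for side effects are reported under outcome a, and self-report is a second adherence measure. The information is therefore not lost. The pill-count percentage still counts the same event twice, and section 4 does not correct that.

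**Conclusion.** The concern holds in two parts of unequal weight. Whether the ratio is per drug or pooled is an ambiguity to be settled. It is not a demonstrated error, and the 200% and 100% figures apply only if pills are pooled. The denominator is a defect on either reading for a participant who stays enrolled after a directed stop: 25% for that drug if per drug, or 125% instead of 200% if pooled. These belong to different readings and should not be combined. Per drug, one such case at day 30 costs a 20-person arm 3.75 points.

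This rests on 120 days of follow-up, one capsule per product per day, and continued enrolment. The documents do not allow the number of such stops to be estimated. No adherence threshold, decision rule or sample size depends on the ratio, so severity is moderate.

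**What to change.** Reword outcome b.ii so that adherence is defined separately for each study product: capsules taken divided by days from first dose to month 4 or to the directed stop of that product, whichever comes first. State the number of capsules per product per day, so that the denominator equals the capsules expected.

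Report the mean for each product and the share of participants adherent to both, with the cut-off for that share fixed in advance. Report persistence separately, as the share still taking each product at month 4, so that directed stops stay visible without being scored as missed doses. If a single combined percentage is also wanted, divide by the capsules expected across both products.

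The cost is outcome wording, the stop date for each product, and counting the two products separately at a pill count already planned. No dose, visit or stopping rule changes, and the power calculation is unaffected.
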